### Randomization

Any patient meeting the inclusion criteria and not violating the exclusion criteria may participate in the EARLYDRAIN study and be randomized to either receive a lumbar drain or not, thus defining the two distinct groups LD and NoLD.

Randomization is performed via a dedicated internet site accessible for all local investigators of the participating trial centers http://www.randomizer.at. No stratification or minimisation is to be used. The security measures of the online randomization system "randomizer.at" include that 1. All transactions are logged, 2. The audit trail of the trial can be accessed and analysed any time by the trial monitoring committee. 3. Network traffic between the web-browser and the randomizer is encrypted using SSL (*Secure Sockets Layer*) with strong encryption.

### Sample size calculation

In the ISAT trial, the largest trial on the treatment of aneurysmal subarachnoid hemorrhage so far, the mortality at one year follow-up was 8.1% to 10.1% [16]. Given the data from both retrospective studies on lumbar drains after SAH, a reduction from 15% to 2.1% after coiling and from 5% to 3% after clipping was shown. Thus, both studies were way lower in their mortality rate and, therefore, their external validity may be questioned.

In the two retrospective trials, 167 [12] and 107 [13] patients were studied, respectively. The effect of lumbar drainage was a decrease of the incidence of "clinical vasospasm" by 34% [12] and 40% [13], respectively.

In the above-mentioned studies the term "clinical vasospasm" includes neurological deterioration not explainable by hemorrhage, cerebral edema, hydrocephalus, hyponatremia, drug toxicity, infection or seizures. No distinction is made between delayed cerebral ischemia (DCI) and vasospasm as potential causes of the clinical worsening.

The following statistical calculations are based on the assumption that the clearly defined subtype of "delayed neurological deficit" measured in the above-mentioned two retrospective trials is highly correlated with clinical outcome 6 months after SAH, which constitutes the primary endpoint of the EARLYDRAIN study.

For lack of previous studies assessing clinical outcome after lumbar drainage in SAH as a primary endpoint this assumption seemed justified.

To assess a decrease of the incidence of DND from 40% to 20% in a prospective clinical trial, 93 patients in each of the two study arms are required to gain a power of 85%, using an alpha error of 5%. To account for possible imbalances in the randomization procedure concerning severity of clinical and radiological grading of the SAH or the choice of treatment and to facilitate a preplanned analysis on the severity of the initial hemorrhage, the planned study size is to include and randomize altogether 300 patients. This results in a power of 85.2%, again, using an alpha error of 5%, to detect a decrease in the rate of severe disability on a dichotomized modified Rankin scale from 50% to 33%, which would be consistent with the effect size from the retrospective trials on a dichotomized GOS [12,13]. The EARLYDRAIN investigators are aware of other, more conservative calculations for the sample size of patient-centered outcome studies targeting vasospasm, indicating that there may be the necessity to include more than 5000 patients in a single trial [17]. The power calculations, as described above and based on the available retrospective data, do not substantiate numbers this large. Besides feasibility issues, clinical experience from the principal investigators considering the expected effort-benefit ratio does not warrant enlargement of the trial to detect a rather small difference between groups.

### Safety of lumbar drains after aneurysmal SAH

In the above-mentioned two retrospective studies, mortality was lower in the lumbar drainage group. Neither of the retrospective studies mentions procedural related complications for the lumbar drains [12,13]. In patients with increased intracranial pressure, careful lumbar drainage of CSF may be a possible treatment even in case of compressed basal cisterns [14]. A feasible strategy to enhance safety is determination of the lumbar-cranial pressure gradient and cessation of lumbar CSF diversion in patients with increasing pressure difference [15].

However, in patients presenting increased intracranial pressure or compressed basal cisterns on CCT-scan the risk associated with lumbar drainage is unclear according to the current state of medical knowledge. In unclear cases the investigator must refrain from the insertion of a lumbar drain.

### Outcome assessment

The primary endpoint is disability after 6 months, assessed by the modified Rankin Scale [18] dichotomized at a score of 0 to 2 versus 3 to 6 (6 = death). Assessment is performed by a blinded investigator of the local study center by personal visit. Alternatively, a telephone questionnaire is suitable for outcome assessment using the modified Rankin Scale [19]. Outcome assessment is planned to be done on the whole dataset as well as in preplanned stratified subsets (i.e. for example clinical SAH grade according to the Hunt&Hess scale 1-2 vs. 3-5 [20], CT grading according to Fisher I-III vs. IV [21]).

Secondary outcome criteria are:

• Mortality after 6 months

• mRS score after 6 months as continuous variable

• Angiographic vasospasm on day 7 to 10, as defined by a caliber reduction by 33% or more compared to the initial digital subtraction angiography

• Endovascular rescue therapy performed due to proven vasospasm, using balloon dilation of spastic vessels and/or arterial infusion of vasodilators

• Infarction (due to vasospasm) in the last CT scan before discharge

• Expression of clinical delayed neurological deficit after the aneurysmal SAH until discharge from acute care.

• Daily course of TCD mean flow velocity in both MCA at a depth of 50-60 mm

• Rate of death during the initial hospital treatment after the aneurysmal SAH.

• Rate of CSF shunt insertion during the first six months

• Presence of CSF infection during the first 14 days, as defined by modified CDC criteria for device-associated meningitis (treatment required on either positive culture, or elevated cell count, red cell/white cell ratio, increased lactate and/or decreased glucose) [22].

The following parameters will be recorded and used in predictor-/association models concerning primary and/or secondary outcome parameters:

• Gender

• Age

• Hunt&Hess grade on admission

• Time from symptom onset to admission

• Location of aneurysm

• Time from symptom onset to aneurysm treatment

• Treatment of aneurysm by clipping or coiling or both

• Time from symptom onset to randomization

• Time from symptom onset to treatment start (i.e. insertion of the lumbar drainage in the treatment arm)

• Time from admission to discharge

• Insertion of EVD (yes/no)

• Duration of EVD being in place

• Duration of lumbar drainage

• Amount of CSF drained by EVD [ml]

• Amount of CSF drained by lumbar drain [ml]

• Use of nimodipine (yes/no)

• Use of statins (yes/no)

• Use of Mg^2+ ^(yes/no)

• Transcranial Doppler ultrasound in both MCA at 50-60 mm depth, 1x daily (> 160 cm/s versus < 160 cm/s)

• Presence of CSF infection during hospital stay (yes/no)

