The aim of the EARLYDRAIN study is to examine the efficacy of application of lumbar drainage in patients with acute subarachnoid hemorrhage from a ruptured cerebral aneurysm. The hypothesis is that early application of a lumbar drain after aneurysmal SAH leads to an improved outcome at six months after the hemorrhage, measured by the modified Rankin score. Furthermore, it is hypothesized that this postulated clinical effect will be due to a diminished incidence of cerebral vasospasm and delayed cerebral ischemia. Therefore the incidence of angiographic vasospasm and the development of new infarctions shown on CCT at discharge of the patient will be among the secondary endpoints of the present study.

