**Figure 1 F1:**
[figure not shown]
**EARLYDRAIN study algorithm**. The EARLYDRAIN study algorithm showing the course of events after the initial aneurysmal subarachnoid hemorrhage (SAH) and the subsequent surgical or interventional aneurysm treatment. The study includes two groups, a treatment group receiving lumbar CSF-drainage (LD) and a control group receiving no lumbar drainage according to protocol (NoLD). The timing of the patient's consent to study participation, randomization, cranial imaging and assessment of clinical outcome is indicated by the shaded boxes. Imaging on day 7 to 10 is scheduled according to local guidelines. If a local center performs no routine cerebrovascular imaging for vasospasm screening in patients without clinical suspicion, it may be omitted.

In patients in the LD-group, CSF drainage via the lumbar drain is started slowly and steadily at a rate of approximately 5 ml per hour after the post-interventional CCT. This leads to a planned daily CSF-drainage of 120 ml per day through the lumbar route. Patients in both groups may receive additional CSF drainage via a ventricular device. The amount of CSF drained via the ventricular route is determined according to clinical requirement and not specified by the study protocol.

In order to enhance accuracy of the amount of CSF drained, regular drainage control every other hour and stopping in case of excess drainage is strongly recommended by the principal investigators. In case of neurological decline suspiciously related to the lumbar drainage, the drain must be closed immediately. Drainage may be gradually restarted after 12 to 24 hours, after performing a CCT scan.

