If the post-procedural CCT or any other follow-up CCT scan shows compressed basal cisterns or any signs of threatening herniation, lumbar CSF diversion in the LD-group must not be performed. It may still be feasible to carefully drain CSF via the lumbar route [14], but this is at the discretion of the local investigator and not recommended. In patients requiring sedation and mechanical ventilation, either due to neurological impairment or for other medical reasons, intracranial pressure monitoring is mandatory. This may be performed according to local policy either with parenchymal or ventricular devices. If the intracranial pressure exceeds 20 mmHg, further CSF drainage via lumbar route shall be interrupted until the ICP is below 20 mmHg again. Careful CSF-drainage via the lumbar route may still be feasible in case of high intracranial pressure [14], but again this is at the discretion of the local investigator. A method of detecting the safety of lumbar CSF diversion may be determining the gradient of lumbar versus intracranial CSF pressure [15]. Albeit promising, the Earlydrain investigators explicitly rate this approach preliminary and experimental. In case of doubt, lumbar CSF diversion must not be performed.

Further neuromonitoring with transcranial duplex sonography (TCD), electroencephalography (EEG), brain tissue oxygenation recordings, jugular bulb oxymetry, regional cerebral blood flow measurement, microdialysis or other methods is at the discretion of the center and according to its local guidelines. As far as possible, this data should be saved electronically for post-hoc analysis.

A CCT scan as well as conventional digital subtraction angiography (DSA), CT angiography or MR angiography for assessment of vasospasm in the larger vessels is routinely performed on day 7 to 10 after the initial hemorrhage, according to local guidelines. In case of the occurrence of a DND when vasospasm is assumed to be the cause, angiography may be performed at any time. If it is performed earlier than day 7 to 10 and the patient shows no clinical deterioration thereafter, the angiography on day 7 to 10 is omitted. Treatment of radiographically confirmed vasospasm is according to local guidelines and not specified in the Earlydrain study protocol. It may include augmentation of cerebral blood flow via hypertensive hypervolemia as well as endovascular balloon dilation or intraarterial infusion of vasodilators.

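### The vasospasm endpoint is tied to day 7 to 10, but the imaging rules drop that image after an early angiogram if no deterioration follows and let some centres skip it, so proven early cases can go uncounted

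*Protocol article*

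**What the plan says.** Four places in the protocol article bear on this point.

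- **Outcome assessment** lists as a secondary outcome "Angiographic vasospasm on day 7 to 10, as defined by a caliber reduction by 33% or more compared to the initial digital subtraction angiography". The window is part of the definition.
- **Interventions** opens a route to earlier imaging: "In case of the occurrence of a DND when vasospasm is assumed to be the cause, angiography may be performed at any time". Where an angiogram was taken before the window and "the patient shows no clinical deterioration thereafter, the angiography on day 7 to 10 is omitted", no second image follows. This is worded as a rule, not an option. The same section foresees imaging before day 7 when it sets the end of drainage.
- **The Figure 1 legend** leaves timing to the centres ("Imaging on day 7 to 10 is scheduled according to local guidelines") and adds: "If a local center performs no routine cerebrovascular imaging for vasospasm screening in patients without clinical suspicion, it may be omitted".
- **Background**, in the statement of aims, gives the endpoint its role: "it is hypothesized that this postulated clinical effect will be due to a diminished incidence of cerebral vasospasm and delayed cerebral ischemia". It names the incidence of angiographic vasospasm among the secondary endpoints without any time window.

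No section says that an early angiogram counts toward the endpoint.

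**The concern.** Take a patient with a deficit on day 5 whose angiogram shows vasospasm and who then stays stable. Under Interventions there is no later angiogram. Under Outcome assessment there is then no image in the window, so a proven case is either missing or counted as free of vasospasm.

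This loss is not random. Early imaging is triggered by DND, and the sample size section assumes that DND halves with drainage, from 40% to 20%. Whether a patient has an evaluable image therefore depends on a post-randomisation event that is expected to differ by arm.

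The legend's rule adds a second selection. In centres without routine screening, only patients under suspicion are imaged. The article describes blinding only for the 6-month Rankin assessment, and no sham drain is mentioned, so those who form the suspicion can see the allocation.

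At stake is one of the endpoints meant to show whether a clinical benefit works through less vasospasm.

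**Working it through.** **The plan's own figures.** The article gives none for vasospasm. The DND rates used below come from its first sample size statement ("To assess a decrease of the incidence of DND from 40% to 20% in a prospective clinical trial, 93 patients in each of the two" arms), which reproduces at 85% power, two-sided 5%, without continuity correction:

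n = [1.960·√(2·0.30·0.70) + 1.036·√(0.40·0.60 + 0.20·0.80)]² / 0.20² = 92.7, so 93 per arm.

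This confirms the input. It says nothing about the vasospasm endpoint.

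**Illustration A: early-imaged patients leave according to vasospasm status.** Let p be the true rate, e the share of positives imaged early only, and f the share of negatives imaged early only. The rate among patients with a window image is

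p(1−e) / [p(1−e) + (1−p)(1−f)].

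All inputs are assumptions. p = 50% control and 33% drainage are the article's Rankin rates, borrowed for want of a vasospasm rate. e = 40% and 20% are its DND rates, borrowed as early-imaging shares.

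| Handling | Control | Drainage | Difference (points) |
|---|---|---|---|
| Full ascertainment | 50.0% | 33.0% | 17.0 |
| Only positives leave (f = 0) | 0.30/0.80 = 37.5% | 0.264/0.934 = 28.3% | 9.2 |
| Negatives leave at half the rate (f = 20%, 10%) | 0.30/0.70 = 42.9% | 0.264/0.867 = 30.5% | 12.4 |
| Negatives leave at the same rate (f = e) | 50.0% | 33.0% | 17.0 |
| Early positives counted as non-events, p(1−e) | 30.0% | 26.4% | 3.6 |

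With equal true rates (50% in both arms) and the same e, drainage looks worse by 6.9 points (37.5% vs 44.4%) if f = 0, by 4.2 points (42.9% vs 47.1%) if negatives leave at half the rate, and by nothing if f = e.

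**Illustration B: patients leave according to DND, and both routes operate.** DND is 40% vs 20%, as in the article. Assume vasospasm in 80% of DND and 20% of other patients, so the full rates are 0.40·0.80 + 0.60·0.20 = 44% and 0.20·0.80 + 0.80·0.20 = 32%, a difference of 12.0 points. Let d be the share of DND patients with an early image only and s the share of non-DND patients never imaged.

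| d | s | Control | Drainage | Difference (points) |
|---|---|---|---|---|
| 25% | 0 | 40.0% | 29.5% | 10.5 |
| 50% | 0 | 35.0% | 26.7% | 8.3 |
| 75% | 0 | 28.6% | 23.5% | 5.0 |
| 0 | 30% | 49.3% | 35.8% | 13.5 |
| 0 | 60% | 57.5% | 43.1% | 14.4 |
| 50% | 30% | 39.4% | 29.1% | 10.3 |
| 50% | 60% | 47.3% | 34.3% | 13.0 |

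Worked row (d = 50%, s = 0): control (0.20·0.80 + 0.60·0.20)/0.80 = 35.0%; drainage (0.10·0.80 + 0.80·0.20)/0.90 = 26.7%. With 150 per arm (an equal split of the 300 is assumed), 120 and 135 patients remain.

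The early-imaging route shrinks the difference and the skipping route widens it. Together they can land on either side of the true 12.0 points. With vasospasm probabilities of 70% and 30%, the full difference is 8.0 points and falls to 7.0, 5.6 and 3.4 at d = 25%, 50% and 75%.

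**The case against.** The best defence is a benign reading. Interventions makes the day 7 to 10 image the routine vasospasm assessment and drops it when an earlier one exists, so the early image may be meant to stand in for it. Background names vasospasm incidence without a window, which fits. The handling of absent images may also sit in a full protocol or analysis plan that is not shown. This is plausible as intent, but the definition as written excludes the early image. Counting it would change the stated endpoint rather than fill in a detail. Nor can any later plan recover images that were never taken.

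Three stronger readings are tempting and not supported.

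- A reader might infer that the most informative patients are lost throughout. That fits only the early-imaging route, and only patients without later deterioration. The legend's rule loses low-suspicion patients.
- A reader might infer that the comparison is biased in a known direction, or would reverse. The reversal above needs borrowed rates and positives leaving more often than negatives. Interventions omits the later image after any early angiogram without deterioration, positive or negative, and the other route pushes the opposite way.
- A reader might infer that the mechanistic question fails altogether. Background also names new infarction on CT, and Outcome assessment adds endovascular rescue for proven vasospasm, DND until discharge and daily Doppler velocities. None of these needs a day 7 to 10 angiogram.

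The mix of imaging modalities adds little. The definition fixes the baseline as the initial DSA but not the follow-up method, so reporting modality is enough.

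**Conclusion.** The conflict between the endpoint definition in Outcome assessment, the omission rule in Interventions and the Figure 1 legend is certain from the text. Followed literally, the plan leaves uncounted some vasospasm proven before day 7, and the chance of this depends on DND, which is expected to differ by arm.

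The size and net direction are not known. Under the borrowed rates in Illustration A, the early-imaging route alone takes 17 points to about 9 to 12 when negatives leave not at all or at half the rate of positives. There is no complete-case bias if both leave equally. The skipping route raises observed rates.

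This is one of ten secondary outcomes, and the primary modified Rankin endpoint is untouched. It should be corrected, but it does not threaten the trial's main conclusion.

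**What to change.** Reconcile the three places through the endpoint definition:

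- Define the endpoint as a caliber reduction of 33% or more versus the initial DSA on any angiogram after aneurysm treatment up to day 10, so that an early angiogram counts.
- Report imaging rates, timing and modality by arm.
- Have each centre declare beforehand whether it images all randomised patients, and add a sensitivity analysis restricted to centres that do. A practice declared in advance does not depend on allocation, so the randomised comparison within those centres is preserved.

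The cost is a change of wording and one centre-level field. No extra imaging is needed, and no change to the imaging schedule or to care is proposed.

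There are two drawbacks. Patients imaged more than once have more chances to be positive; since repeat imaging follows deterioration, this may occur more often in controls, and the report of imaging by arm would show it. The sensitivity analysis will also be smaller, and it is the only part of the fix that addresses images never taken.

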#### Data Management and Monitoring Body

All data specified in the trial protocol will be documented in the patient's records and on standardised Case Report Forms (CRFs), available as original with two copies. The investigating physician is responsible for appropriate completion of the form. The (CEHRIS) of the Center for Stroke Research Berlin (CSB) is responsible for data base development, data acquisition via double entry, data storage, and validation. Data validation includes controls of completeness, consistence and plausibility of the data documented in the CRF using a query system between data management and investigating physician. After resolution of all queries concerning enrolled patients, the data bank is closed (end of the trial) and forwarded to the biometrician for the purpose of evaluation. After finalization of all evaluations the final report and all original CRFs are delivered to the principal investigator.

The trial is supervised and monitored by the Intensive Care Treatment of Stroke group (ICTOS) of the CSB including initiation and regular site visits, source data verification, and reports of adverse events. All data management and supervising procedures are performed according to Standard Operation Procedures (SOPs) of the CSB and in accordance to ICH-GCP Guidelines (E6) and the declaration of Helsinki.

### Adverse events (AE) and severe adverse events (SAE)

Apart from AE and SAE which may occur after the beginning of the trial (synchronous with the insertion of the LD) there are complications related to securing the aneurysm:

Surgery-related complications: Surgical treatment includes the known risks of surgical interventions.

Complications related to endovascular therapy: Endovascular therapy includes the risks known to be associated with it.

### Definition of adverse events and severe adverse events

The term "adverse event" (AE) describes any sign, symptom, syndrome or any disease 1. occurring newly in a trial participant after consent to the trial and 2. being of particular interest for the assessment of the disease or the security of the therapeutic concept. In this trial AEs include:

• Arterial or venous thrombosis,

• Complications related to insertion of a lumbar drainage,

• Any SAE

The term AE does not implicate a causal correlation with the participation in the trial. Surgical or endovascular interventions are not necessarily considered as AE but can be necessary for the therapy of an AE. AEs are divided in severe (SAE) and non-severe (AE) adverse events.

An SAE is any AE occurring during the trial that is related to:

• Death

• Any life-threatening condition,

• Re-hospitalisation or prolongation of hospitalisation,

• Long-term or severe restraint of the state of health, or

• Birth deformities.

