### Documentation

Investigation of AEs is part of every assessment of the study participants. Any AE has to be documented in the CRF.

Every SAE has to be documented on a special documentation form and has to be reported within 24 hours after recording, but at least at the next working day, to the data monitoring center in Berlin.

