#### Data and Safety Monitoring Board (DSMB)

Safety aspects of the trial are supervised by the DSMB. The DSMB consists of an independent stroke physician, a neurosurgeon, and a neurointensivist, neither involved in the planning nor conduction of the trial nor participating in the trial. The DSMB independently elects a chairman. The DSMB is responsible for critical evaluation and suggestions for improvement of the trial protocol and supervision of the trial course. The DSMB has to be informed about the results of safety issues, especially the number of AEs and SAEs in each treatment group at least after every 10 patients having been enrolled, but at least every 6 months starting with the day of inclusion of the first patient, but also whenever the Steering Committee believes this to be necessary. Based on the results of safety aspects the DSMB will recommend to continue or stop the trial. The members of the DMSB confer personally or via telephone and report their recommendations to the Steering Committee.

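### The AE and SAE definitions are circular and carry an undefined interest test, so serious non-fatal events without an endpoint of their own can be left out of expedited reports and DSMB counts

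*Protocol article*

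**What the plan says.** All of this is in the protocol article.

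- *Definition of adverse events and severe adverse events* sets two conditions for an AE, joined by 'and'. The event must be "occurring newly in a trial participant after consent to the trial", and it must be "being of particular interest for the assessment of the disease or the security of the therapeutic concept". The section then lists what AEs include: thrombosis, complications of inserting the drain, and any SAE. It adds that calling something an AE implies no causal link with trial participation.
- The same section defines the serious class: "An SAE is any AE occurring during the trial that is related to" death, a life-threatening condition, readmission or a longer stay, lasting or severe impairment, or birth deformity. It also states that "AEs are divided in severe (SAE) and non-severe (AE) adverse events".
- *Documentation* requires every AE to be entered in the CRF. For serious ones: "Every SAE has to be documented on a special documentation form and has to be reported within 24 hours after recording", or at the latest on the next working day.
- *Data and Safety Monitoring Board (DSMB)* says that the board is told the results on safety, "especially the number of AEs and SAEs in each treatment group at least after every 10 patients having been enrolled", and at least every six months. It recommends continuing or stopping on safety results.
- *Outcome assessment* states blinding for the six-month mRS only: "Assessment is performed by a blinded investigator of the local study center by personal visit". It also lists "Mortality after 6 months" and death during the initial hospital stay as secondary outcomes.

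**The concern.** Whether an event is serious should follow from what happened to the patient. Here a serious event must first qualify as an AE, and that depends on a relevance judgement with no stated criteria. The reporting duty and the by-arm counts both inherit that judgement.

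The people who would make it are not blinded in any way the article describes. One arm has a visible lumbar drain, the other should not have one before the day 7 to 10 imaging, and no sham is mentioned. A discretionary filter applied with knowledge of the arm could hide a safety difference or create one. The DSMB relies on these counts when it advises whether the trial goes on.

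There is also a labelling problem. AE means the whole set in one sentence, since it includes every SAE, and only the non-severe part in another.

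**Working it through.** No figure in the document bears on this point, so the check is mainly a reading of the passages side by side.

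**Step 1: the logic.** Write N for new after consent, I for meeting the interest condition, and S for meeting a seriousness item.

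- General AE definition: AE = N and I.
- SAE definition: SAE = AE and S. Substituting gives SAE = N and I and S.
- The list item adds that every SAE is an AE. Since SAE is already a subset of AE, this adds no new event. An event with N and S but not I is outside both sets before the list item is applied, and still outside afterwards.

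The item signals an intent to include every serious event, but it supplies no independent rule for a site to apply.

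**Step 2: what inherits the filter.** The 24-hour duty in *Documentation* attaches to SAEs. CRF recording there attaches to AEs. The DSMB counts are of AEs and SAEs. All three depend on I.

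**Step 3: who decides.** The article does not say who decides on I. *Documentation* puts AEs in the CRF, and *Data Management and Monitoring Body* makes the investigating physician responsible for completing it. That the physician knows the arm is an inference from *Interventions* and *Amount and duration of CSF drainage*; the article does not say so.

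**Step 4: what is collected by another route** (*Outcome assessment*, *Interim Analysis*).

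| Serious event | Route independent of the AE definition |
|---|---|
| Death | mRS 6 in the primary endpoint; two mortality endpoints; in-hospital death singled out in the interim safety analysis |
| Delayed neurological deficit, infarction due to vasospasm, CSF infection, shunt insertion, endovascular rescue | Secondary endpoints |
| Thrombosis, complications of drain insertion | Named in the AE list |
| Longer stay | Time from admission to discharge is recorded for the predictor models, but not as a safety event |
| Readmission; life-threatening systemic illness such as pneumonia | None stated |

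The real exposure is therefore in the last two rows. For the first two, what can be lost is the expedited report and the place in the SAE tally.

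**Step 5: the double label.** With s serious and n non-severe events in an arm, the number of AEs is n + s under the list and n under the sentence that divides the classes. The DSMB section does not say which is meant.

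**Step 6: size, as illustration only.** Assume the same true risk p in both arms, full capture in one arm and a fraction c in the other. The false difference is p − pc = p(1 − c). None of these inputs comes from the document.

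- p = 0.20, c = 0.90: 0.20 × 0.10 = 0.02. Per 150 patients (half of the planned 300, taking equal arms), 30 against 27 events.
- p = 0.40, c = 0.70: 0.40 × 0.30 = 0.12, or 60 against 42 events.

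A range of 2 to 12 percentage points merely restates the assumed capture rates. It shows how the mechanism works and is no evidence that it operates here.

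**The case against.** The best defence is that the list item shows what was meant: any event meeting a seriousness criterion is treated as an AE. Nothing tells sites to screen serious events for interest. The interest condition also has two limbs, and the one on assessing the disease applies to both arms alike. A grave event after subarachnoid hemorrhage is hard to call irrelevant to the disease, and lack of a causal link is expressly no ground for exclusion. Site visits, source data verification and data queries run under ICH-GCP. The DSMB is not confined to the AE and SAE numbers. Instructions in the CRF or SOPs may be clearer than this article.

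Much of this stands. A reader might infer that deaths can disappear from the trial; the endpoints and the interim analysis rule that out. A reader might also infer that the filter favours one arm because a therapeutic concept under test exists only with the drain. The disease limb answers that, and differential judgement remains conjecture. The double label is minor, since any overlap would follow the same rule in both arms.

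What does not stand is that the intent cures the text. Monitoring checks records against the protocol's own definition, so an event outside that definition is not a discrepancy. Nor is this a detail left to a fuller document: the article prints the definition, and as printed it is circular.

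**Conclusion.** The concern holds in limited form. The definitions are circular and ambiguous, and they place an unspecified relevance test in front of seriousness. They do not amount to clear permission to withhold reports. The practical exposure is serious non-fatal events with no endpoint of their own, which could be missing from the 24-hour reports and the by-arm DSMB counts. For deaths, only the expedited report and the SAE tally are affected.

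The size cannot be derived from the document, and neither can a direction of bias. The conclusion rests on a literal reading and on two inferences: that the investigating physician applies the condition, and that the drain makes the arm visible. The planned endpoint analyses are not touched.

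**What to change.** - Define an SAE directly: any new untoward event after a start of observation common to both arms that meets one of the listed seriousness criteria. State that this applies regardless of the interest condition or any presumed relation to the drain, and identically in both arms.
- Fix that common start explicitly. *Adverse events (AE) and severe adverse events (SAE)* ties the beginning of the trial to insertion of the drain, which controls do not receive by protocol at that point, while the definition section counts from consent. The two should be reconciled.
- Keep the interest condition for non-severe AEs only.
- Report SAEs and non-severe AEs to the DSMB as separate, non-overlapping classes.

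The cost is a change of wording in the protocol and the CRF instructions, and some additional SAE forms.
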